## Hypothesis

**Our null hypothesis  $H_0$**  states that exercising with a cloth mask will be inferior to the current standard of exercising without a facemask, limiting peak exercise when non-inferiority margin is 1 estimated metabolic equivalent ( eMET  $3.5 \text{ mlO}_2 \cdot \text{kg}^{-1} \cdot \text{min}^{-1}$ ).

**Our alternative hypothesis  $H_1$**  states that exercising with a mask will not be inferior to the current standard of exercising without a facemask, limiting peak exercise when non-inferiority margin is 1 eMET.

## Specific Aims

### 1) To gain further understanding on effects exercising with a cloth mask has on exercise capacity.

Our working hypothesis is that wearing a face mask will limit exercise capacity by a minimal clinically important difference (MCID) of 1 estimate metabolic equivalent (eMET).

## EXPERIMENTAL DESIGN & METHODS

**Subject Recruitment:** We will recruit 20 subjects through the Cleveland Clinic. Inclusion Criteria: Healthy subjects age  $\geq 18$ , Exclusion Criteria: Any long-term disease that would interfere with their ability to exercise safely, fever  $\geq 100.4$  F, or pregnancy. Informed consent will be obtained by the CoPI, and need for medical clearance determined based on ACSM's 2015 preparticipation guidelines. (See appendix 12.6) To remain compliant with enterprise guidelines we will not be recruiting healthy subjects outside of the Cleveland Clinic staff at this time to avoid increase COVID-19 exposure risk. However, if the enterprise changes the guidelines we will expand our enrollment to include non Cleveland Clinic employees. Employees will not be solicited by

direct initiation. Recruitment will involve only posted notice or general advertising that does not pressure employees into participating for fear of job loss, delayed promotion, or other influences from their superior.

**Study Design:** The study design is a prospective crossover non-inferiority trial where subjects will complete 3 separate graded exercise treadmill tests each time wearing either No Mask, N-95 Mask (3M), or Cloth Mask (Boco). The order of the mask worn will be randomly assign to minimize familiarization or training effect. All testing will be performed in a Cleveland Clinic facility following standardized COVID-19 screening precautions. We will compare the data collected from each test to asses for differences between subject comfort, peak exercise capacity (eMET), heart rate response during exercise and recovery.

**Testing:** After completing the informed consent and being medically cleared, subjects will then perform a symptom limited graded exercise treadmill test using a modified Balke protocol. The modified Balke, which is a well-accepted treadmill protocol that keeps the speed constant and increases workload by grade. Subjects will rest for 3 minutes and resting heart rate, blood pressure, subjective perceptions of the face mask will be measured. Subjects then will walk at 0% grade at 3 miles per hour for 2 minutes. Elevation will be increased by 2% after the initial 2 minutes and by 1% each minute thereafter until the test is terminated. Heart rate will be monitor by Polar H10 heart rate monitor and oxygen saturation will be measured with a pulse oximeter. We will continue to monitor heart rate during recovery at 1, 3 and 5 minutes post exercise. We will monitor each stage for perceived exertion, feelings of light headedness, anxiety, and discomfort. The test will also be terminated at the request of the subject or if any chest pain develops. The scale of measuring subjective perceptions instrument will be adminstereted after collecting 5 minutes of resting, end of the exercise test, and at 5 minutes post recovery. The graded exercise test will be performed once with No Mask, once with 3M 8200 N-95 Respirator, and once with a Cloth Mask (Boco). Subjects will be randomized by a random number generater (1= No Mask, 2= N-95, 3= Cloth Mask) to determine the order the perform each exercise test No Mask, N-95 or Cloth Mask and will complete the other tests 2 atleast 1 day apart. Subjects will be instructed to abstain from exercise for 2 days before the test.

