## Project Timeline

All testing expected to be completed within 2 weeks, followed by data and statistically analysis. We intend to have this study written up and published prior to the opening of public gyms in Ohio.

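### The 1-day minimum gap between tests is shorter than the 2-day exercise abstention, so the protocol permits a study test inside its own rest window

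*Protocol*

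**What the plan says.** In Experimental Design & Methods, the Study Design paragraph states that "subjects will complete 3 separate graded exercise treadmill tests each time wearing either No Mask, N-95 Mask (3M), or Cloth Mask (Boco"). The Testing paragraph describes each of these as a "perform a symptom limited graded exercise treadmill test using a modified Balke protocol".

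The same paragraph fixes the spacing and, in the next sentence, the rest rule: subjects "will complete the other tests 2 atleast 1 day apart. Subjects will be instructed to abstain from exercise for 2 days before the test". The stray numeral most likely belongs to the phrase for the two remaining tests and does not alter the 1-day minimum.

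Two other statements bear on the point. Study Design says "The order of the mask worn will be randomly assign to minimize familiarization or training effect", and Project Timeline says "All testing expected to be completed within 2 weeks".

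**The concern.** Two adjacent sentences give different time limits for the same thing, namely how recently a subject may have exercised before being tested. The spacing rule accepts one day and the rest rule asks for two. A symptom-limited treadmill test is plainly exercise, so a schedule at the spacing minimum cannot satisfy the rest rule for tests 2 and 3.

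What is at stake is residual fatigue that can be present at tests 2 and 3 but not at test 1. In a crossover each subject is compared with themselves, so unequal preparation between tests enters the within-subject difference directly. The protocol's own rest rule shows that recent exercise was judged to matter. Peak capacity is not the only outcome exposed: heart rate in exercise and recovery, perceived exertion and the comfort scale, which includes items on fatigue and feeling unfit, could plausibly be affected too. The effort-related outcomes also have no wide non-inferiority margin to absorb extra noise.

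**Working it through.** The protocol gives no figure on this point to reproduce. The check has three parts: the calendar, the effect on the comparison, and the room in the timeline.

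**Inputs from the protocol.** Three tests per subject and 20 subjects; minimum gap 1 day; abstention 2 days; testing period 2 weeks (14 days); margin 3.5 mL/kg/min, variance 3.5, true difference 0, power 0.90, 5% drop-out and two-tailed 0.05 (Statistical Analysis).

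**Assumptions.** The fatigue loss f at tests 2 and 3 is not in the documents; 0.5, 1 and 2 mL/kg/min are used as a range. The stated variance of 3.5 is used as the variance of the paired difference. As a less favourable case, 3.5 is treated as a standard deviation, giving a variance of 3.5² = 12.25.

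**1. Calendar.** Tests fall on days 1, 1+g and 1+2g for a gap of g days.

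| Gap g | Test days | Breach if 2 days means 48 hours | Breach if 2 days means two full exercise-free days |
|---|---|---|---|
| 1 | 1, 2, 3 | tests 2 and 3 | tests 2 and 3 (test 3 has both earlier tests in its window) |
| 2 | 1, 3, 5 | none | tests 2 and 3 |
| 3 | 1, 4, 7 | none | none |

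If everyone is booked at the minimum, 2 × 20 = 40 of 3 × 20 = 60 tests fall inside the window.

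**2. Effect on the cloth minus no-mask difference.** Let test 1 carry no fatigue and tests 2 and 3 each carry a loss f. Over the six possible orders:
- cloth first (two orders): shift +f
- no mask first (two orders): shift −f
- N-95 first (two orders): shift 0

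The mean shift is (2f − 2f + 0)/6 = 0. The mean square is (2f² + 2f²)/6 = 0.667f², which is the variance added to the paired difference. There is no expected bias, but in a single sample of 20 randomly ordered subjects the chance shift in the mean difference has standard deviation √(0.667/20) × f ≈ 0.18f.

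Power is for the paired non-inferiority test by the noncentral t, with n = 20 × 0.95 = 19, margin 3.5, true difference 0 and one-sided 0.025 (half of the two-tailed 0.05). The noncentrality is 3.5/√(variance/19).

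| f (assumed) | Added variance | On 3.5: total, increase | Power | On 12.25: total, increase | Power |
|---|---|---|---|---|---|
| 0 | 0 | 3.50 | >0.999 | 12.25 | 0.984 |
| 0.5 | 0.17 | 3.67, +5% | >0.999 | 12.42, +1% | 0.983 |
| 1 | 0.67 | 4.17, +19% | >0.999 | 12.92, +5% | 0.980 |
| 2 | 2.67 | 6.17, +76% | >0.999 | 14.92, +22% | 0.962 |

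The planned 0.90 is kept throughout.

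**3. Room in the timeline.** A subject's three tests span 1 + 2g days, and the first must fall no later than day 14 − 2g. For g = 1, 2 and 3 the span is 3, 5 and 7 days, and the latest first test is day 12, 10 and 8.

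**The case against.** The strongest reply is that the two sentences can both be obeyed. The 1-day gap is a floor, and any longer gap satisfies both rules. If the abstention covers every test and all exercise, it is simply the stricter rule and sets the effective minimum; if it does not, there is no breach. The text refers to a single test, and an instruction to subjects can be read as covering only their own exercise outside the study. If the spacing phrase means one clear day between tests, a 48-hour abstention is just met. No sentence actually schedules tests one day apart, and the two-week period does not force it.

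These readings are possible, but the text states none of them, and none leaves the paragraph sound:
- If the abstention governs, the written 1-day minimum is wrong.
- If it covers only the first test, tests 2 and 3 are run under different preparation from test 1.
- If it covers only outside exercise, a symptom-limited test the day before is allowed while ordinary exercise is not.
- If one clear day is meant, two full exercise-free days are still not provided.

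The reply is right about size. The fatigue effect is assumed. At f = 2 it would be 2/3.5 = 57% of the margin, which nothing in the documents supports, so the +76% is hypothetical. The count of 40 of 60 requires every subject to be booked at the minimum. The added variance also assumes no adjustment for test order. The protocol plans mixed models for repeated measures, and whether they include a period term may properly be left to the SAP.

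**Conclusion.** The concern holds. As written, the minimum gap permits a schedule that breaches the rest rule before tests 2 and 3, on the reading that the rule applies before each test and that a study test counts as exercise. Nothing in the protocol says otherwise.

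The consequence for the primary result is small. With randomised order and a fatigue effect common to all masks, no bias is expected. The cost is extra noise of unknown size, which over the assumed range leaves power at 0.96 or above. It is unlikely by itself to change the non-inferiority conclusion. The case for acting is that a badly fixed rule of trial conduct can be put right at almost no cost, before staff book visits from it.

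**What to change.** Replace the two sentences in Testing with one rule: subjects abstain from exercise for 2 days before each of the three tests, and consecutive tests are at least 48 hours apart. If two full exercise-free days are intended, make the minimum 3 calendar days instead. The sponsor should choose one of these and state it.

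The cost is slightly tighter scheduling. Each subject needs 5 days (2-day gap) or 7 days (3-day gap) instead of 3, and all 20 first tests must be done by day 10 or day 8 of the 14. The sample size and the analysis do not change.

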**Mask:**

3M 8200 N-95 Respirator obtain from a third party provider. N-95 Respirators have been purchased outside the Cleveland Clinic supply chain. Cloth Face Mask manufactured by Boco is a custom designed two-layer face masks are built with a tightly woven polyester outer shell fabric and a soft, breathable performance knit mesh inner lining. Includes a slit pocket where a filter can be added.

**COVID-19 Precautions**

**Subject**

Temperature screening upon entering building to determine specific temp before denying subject access (100.4). COVID screening questions upon entry in to hospital. Questions to include whether subject has come from a household with a COVID + family/friend. Pending COVID test – deny entry until negative result determined. Sanitizers available per current placement on walls all patient areas. (Deemed adequate by HH IP department already). Subjects instructed on procedure for hand sanitizing. Subjects to wear cloth mask/hospital-provided mask upon entry and exit. Advised use during exercise as tolerated. Instruction on mask donning and doffing done prior to class start. Absolutely no visitors. Subjects to be dropped off so as to limit number of people in department. Subjects 6 feet apart. Testing restricted to 39 minutes to accommodate equipment sanitation, education, flow of people entering and leaving. Should subjects use towels, they must be provided by hospital, used solely by subject and disposed of in appropriate hamper by subject. Directional flow signage to/from waiting area-gym-conference room. Subjects to be provided individual baggies with supply of masks. Monitors are assigned to each subject, sanitized before and after subject use.

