Following the severe acute respiratory syndrome (SARS) outbreak that occurred in March 2003, a study by Li et.al. was conducted to investigate the effects of wearing N95 and surgical facemasks by assessing the subjective perception of discomfort and heart rate response to each mask following a walking protocol. Subject completed 3 walking intervals as follows: 20 min at 2.0 mph (3.2 km/h), 10 min at 3.0 mph (4.8 km/h), 10 min at 4.0 mph (6.4 km/h) and resting 10 min between each interval. Subjects rated ten sensations of discomfort: humidity, heat, breathing resistance, itchiness, tightness, saltiness, feeling unfit, odor, fatigue, and overall discomfort, and asked to reply to the question “How do you like the facemask?” by rating on a scale ranging from 0 to 10, with 0 representing “not at all”, 5 representing “acceptable” and 10 representing “very fond of”. In general, the ratings for humidity, heat, breath resistance and overall discomfort increased gradually with time and increase of workload. Surgical facemasks had significantly lower ratings than the N95 facemask, which suggested that when wearing either of the surgical facemasks the subject felt drier, cooler, more able to breathe easily and less uncomfortable than when wearing either of the N95 facemasks. The pattern of changes in mean heart rate amongst these facemasks is similar, reaching peaks at the end of the third exercise session. The subjects had lower mean heart rates when wearing surgical masks than when wearing N95 facemasks. High breathing resistance made it difficult for the subject to breathe and take in sufficient oxygen.

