## Statistical Analysis

Non-inferiority design:  $H_0: \mu_{\text{Mask}} - \mu_{\text{NoMask}} \leq -\delta$  vs.  $H_1: \mu_{\text{Mask}} - \mu_{\text{NoMask}} > -\delta$  where  $\delta > 0$  denote the non-inferiority margin of 3.5, which is a (clinically meaningful) minimal detectable difference. The sample sizes are: Total sample size  $n = 20$   $n_{\text{NoMask}} = (1 + 1/k) * \sigma^2 * ((Z_{1-\alpha} + Z_{1-\beta}) / (d + \delta))^2$   $n_{\text{Mask}} = k * n_{\text{NoMask}}$  where  $\sigma^2$  is the variance, and  $d = \mu_{\text{Mask}} - \mu_{\text{NoMask}}$  is known as the allowable difference, which is the true mean difference between the new treatment (Mask) and the control (NoMask). 1)  $\delta = 3.5 \text{ mlO}_2 * \text{kg}^{-1} * \text{min}^{-1}$  (1 eMET=3.5  $\text{mlO}_2 * \text{kg}^{-1} * \text{min}^{-1}$ ): a (clinically meaningful) minimal detectable difference 2)  $k=1$  : the ratio of the sample size of treatment(mask) group to the sample size of control(NoMask) group 3)  $\sigma^2 = 3.5$ : population eMET change variance 4) power: 0.9 5) 5% expected rate of drop-outs 6)  $d=0$ : Descriptive statistics will be used to characterize the patient cohort. Demographic variables will be described using mean with standard deviations for continuous variables and counts with percentages for categorical variables. The Wilcoxon signed-rank signed test or paired-sample t-test will be used to compare continuous variables between the Mask and NoMask exercise. McNemar's test will be applied to compare categorical variables. Mixed-effected linear regression models will be applied for the repeated measures data. Pearson correlation coefficient will be calculated whenever it is appropriate. Analyses will be two-tailed and performed at significance level of 0.05 with SAS 9.3 software (SAS Institute, Cary, NC).

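### The COVID-19 precautions leave mask use in exercise to tolerance and are not reconciled with the one assigned mask condition per treadmill test

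*Protocol*

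**What the plan says.** In the protocol's Experimental Design & Methods, the Study Design paragraph fixes the exposure by test: "subjects will complete 3 separate graded exercise treadmill tests each time wearing either No Mask, N-95 Mask (3M), or Cloth Mask (Boco"). The Testing paragraph repeats it: "The graded exercise test will be performed once with No Mask, once with 3M 8200 N-95 Respirator, and once with a Cloth Mask (Boco"). The test is symptom limited. It also ends if the subject asks to stop or develops chest pain. Neither paragraph mentions a mask that is lifted or removed.

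The COVID-19 Precautions, under Subject, say: "Subjects to wear cloth mask/hospital-provided mask upon entry and exit. Advised use during exercise as tolerated". The same block limits the session: "Testing restricted to 39 minutes to accommodate equipment sanitation, education, flow of people entering and leaving". The Study Design paragraph brings the visits under such precautions: "All testing will be performed in a Cleveland Clinic facility following standardized COVID-19 screening precautions".

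**The concern.** Mask wear is the exposure under comparison, and peak eMET is set by the workload at which the test ends. The two parts of the protocol give test staff different rules. One says each test is done in its assigned condition; the other leaves mask use in exercise to tolerance.

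If the second rule reached the treadmill, the bias would have a known direction. The Background reports of an earlier walking study that "the ratings for humidity, heat, breath resistance and overall discomfort increased gradually with time and increase of workload". A mask worn only while tolerable is therefore most likely to come off near the peak. Workload gained after that is credited to the mask, which shrinks the deficit and favours non-inferiority, the trial's alternative hypothesis. An analysis plan could not correct this later if nobody noted the lifting at the test.

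**Working it through.** **Step 1. The texts side by side.**

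- Study Design and Testing: one condition per test, each done once, in random order.
- COVID-19 Precautions, Subject: addressed to this study's subjects; mask use in exercise is advised, subject to tolerance; no exception for the tests.
- Other exercise in the study: none scheduled.
- Rule for a lifted mask: none in Testing, Mask or Statistical Analysis. The Significance section tells people who struggle to breathe to lift the mask, but as general advice to exercisers, not as a test procedure.

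The two rules are not reconciled anywhere in the protocol.

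**Step 2. The plan's own figure, used only to choose an SD.** The Statistical Analysis section gives n = (1 + 1/k) × σ² × ((z for 1−α + z for 1−β)/(d + δ))², with k = 1, d = 0, δ = 3.5 and power 0.9. I take α as one-sided 5%.

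- σ² = 3.5 as written: 2 × 3.5 × ((1.645 + 1.282)/3.5)² = 4.9, so 5.
- σ = 3.5: 2 × 12.25 × ((1.645 + 1.282)/3.5)² = 17.1, so 18; 18/0.95 = 18.9, so 19 after drop-out.

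Neither gives exactly 20. The SD reading comes closest. The present point does not depend on this mismatch.

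**Step 3. Size of an assumed lifting pattern.** Assumptions that the protocol does not supply:

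- the usual walking equation, by which each 1% of grade adds 1.8 × speed × 0.01. At 3 mph (80.4 m/min) that is 1.8 × 80.4 × 0.01 = 1.447 mL/kg/min per extra minute, or 1.447/3.5 = 0.41 eMET;
- a true deficit of exactly 1 eMET;
- 5 of 20 subjects gaining unmasked time.

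The test is taken as a paired t-test on 20 subjects at one-sided 2.5%, from "Analyses will be two-tailed and performed at significance level of 0.05".

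Mean shift: 5/20 × 0.5 × 1.447 = 0.181 mL/kg/min for half a minute each; 5/20 × 1 × 1.447 = 0.362 for a full minute each. The chance of declaring non-inferiority comes from the noncentral t distribution with 19 df and noncentrality shift/(SD/√20).

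| Reading of 3.5 | SD of difference (mL/kg/min) | Half a minute each | One minute each | Mean shift that doubles 2.5% to 5% | Same, in total subject-minutes (shift × 20/1.447) |
|---|---|---|---|---|---|
| as the SD | 3.5 | 4.1% | 6.4% | 0.259 | 3.6 |
| as a variance | √3.5 = 1.871 | 6.1% | 12.8% | 0.139 | 1.9 |
| as a variance in eMET² | 1.871 × 3.5 = 6.55 | 3.3% | 4.2% | 0.485 | 6.7 |

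This treats the gain as a uniform shift. When 5 particular subjects gain a full minute, they also add spread, and simulation gives about 6.1% instead of 6.4% (SD 3.5) and about 10.6% instead of 12.8% (SD 1.871).

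**Step 4. Away from the boundary.** Noncentrality is now (distance inside the margin + shift)/(SD/√20), with SD 3.5.

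- True deficit zero, the planning value (distance 3.5): the chance of declaring non-inferiority goes from 98.9% to 99.4-99.7%.
- True deficit 1.25 eMET (distance −0.875): the chance stays at or below 0.5%.

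**The case against.** The strongest reply is that the sentence is not about the study masks. It follows directly on the mask for entry and exit, while the study devices are named separately. The surrounding text is plainly borrowed: it mentions classes, an exercise bike and a rower, none of which this trial uses. The Study Design and Testing paragraphs are the specific instruction and already say each test is done in its assigned condition. A subject who cannot bear the mask may ask to stop, and staff monitor every stage for discomfort. Scoring rules for a deviating test may also stand in an analysis plan or test manual that is not shown.

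Most of this stands, and it rules out several stronger readings:

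- A reader might infer that unmasked walking will be scored as masked eMET. The protocol does not say so; it is silent on the event.
- A reader might infer that the No Mask test would be run masked. The words allow it, but no tester would credibly do it.
- A reader might infer that nothing requires the mask to be worn. Doing a test in a named mask is an ordinary statement that it is worn; what is missing is an explicit rule for lifting.

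The reply does not remove the loose end. The block is addressed to these subjects and sets limits on their test session. If the text was borrowed, it was not adapted to the design. Whether the mask stays on, and whether lifting is noted, is a test procedure that an analysis plan cannot supply afterwards.

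**Conclusion.** The point holds as a minor one: an instruction, probably left over from facility text, is not reconciled with the assigned condition per test. If applied to the tests, it would bias toward non-inferiority. The amount is unknown and probably small.

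The error rates in the table are illustrations, not estimates. They rest on an assumed number of lifters, an assumed gain, an outside walking equation and a true deficit exactly at the margin. A reader might take the 12.8% as the trial's likely error rate. The documents do not support that: it is the most extreme cell, it falls to about 10.6% when actual lifters are simulated, and no lifting frequency is given. With the SD reading closest to the planned size, the range is about 4-6% against a nominal 2.5%. At the planning value of no true deficit, the effect under that reading is immaterial.

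**What to change.** 1. **COVID-19 Precautions, Subject.** Limit the tolerance sentence to time outside the study tests. Add: *During each treadmill test, from the rest period through the 5-minute recovery, the subject wears only the assigned condition.* Rest and recovery belong in the rule because mask perceptions and heart rate are measured then too.
2. **Testing.** Add: *The subject may remove the mask or stop at any time. Removing the mask, or lifting it to breathe, ends the test for scoring; peak eMET and peak heart rate are taken at the last workload before it. The event is recorded.*

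The cost is two wording changes and one field on the test form, with no added visits or measurements. Subjects keep full freedom to take the mask off, so safety is unchanged. The downside is that some masked eMET values will be slightly lower than if lifting were ignored, which makes non-inferiority a little harder to show.
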